## Background

Geriatric patients are characterised by high age, multimorbidity and polypharmacy, frequently in combination with functional impairments [1, 2]. This makes them frail and particularly vulnerable to an increased risk of acute hospital admissions and readmissions [3, 4]. Despite the ongoing demographic change towards more old and oldest olds [5, 6], the number of hospital beds has been reduced markedly [7], mainly achieved by reducing in-hospital length of stay (LOS) [8]. At the Department of Geriatrics, Odense University Hospital (G-OUH) LOS declined from 11 days in 2006 to 6 days in 2023 (personal communication). Consequently, older patients are discharged in a more vulnerable state than previously, but with care support delivered by the municipal home care.

In Denmark, readmissions occur in about 10% of 65 + year old [9] but increases with higher age [10]. The risk of readmission increases with the number of comorbidities, medications and prior contacts to the primary health care providers [10], all being characteristics of the geriatric patient.

For geriatric patients admitted to G-OUH, readmission occurs in 19% of discharged patients according to hospital administrative data, and the median number of days until readmission is nine [11]. Most patients are readmitted with a diagnosis unrelated to their index admission, with pneumonia and dehydration being the most common causes—even when these were not the primary diagnoses at the time of the index admission.[11].

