### Aim

The aim of this study is to investigate the effects of a coordinated and simultaneous home visit 2–5 days after discharge, by a community nurse and a geriatric nurse equipped with POCT equipment on 30-day readmissions.

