**Fig. 1 Fig1:**
[figure not shown]
Study design

Eligible patients are informed about the project (orally and in writing) and invited to join. If they accept, they sign an informed consent. They are randomised on the day of discharge to either the intervention or control group. In the case of a planned discharge during the weekend, the participants are randomised on Friday. Participants randomised to the control group receive a usual discharge, while participants in the intervention group receive a usual discharge as well as a coordinated follow-up visit, which is planned to take place 2–5 working days after the day of discharge.

For all participants (control and intervention), administrative and clinical data will be collected from hospital records and the hospital administrative system, e.g. hospital discharge diagnoses, LOS, medication, medical history, Charlson Comorbidity Index [29] and Barthel Activities of Daily Living (ADL) score.

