### Data analyses

#### Sample power and statistical power

Based on our recent finding of a 28% reduction in readmissions following geriatric follow-up to discharged geriatric patients [42], and using a 2-proportions with 2-sample equality power test, a current readmission rate of 19% (control group), and an expected 28% reduction by the intervention, the readmission rate in the intervention group is (19 − (19 × 0.28)) 13.68%. If the proportions of group A, *pA*, is (100 − 19 =) 81 and proportion of group B,* pB*, is (100 − 13.68 =) 86.32,* α* = 0.05,* β* = 0.80 and* К* = 1, the sample size should include 763 in each group, and 1526 patients totally [43]. The total finally becomes 1832 after accounting for an expected dropout rate of 20%. The Department of Geriatric Medicine at Odense University Hospital is expected to discharge about 1500–1800 patients in 2022–2023 alone, which makes it feasible to include enough participants to reach statistically significant results in 2 years. We had originally calculated a shorter time period for the study, however, due to COVID and nurse shortage, the number of beds has been reduced. We have included statistics for all inclusion and exclusion criteria in our model for estimation of the time required for the study.

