### Statistical analyses

Statistical analyses will be carried out STATA Version 17 (StataCORP LLC, Texas, USA).

We will exclude participants with single-item missing data relevant to the analysis and will not perform imputations. An intention-to-treat analysis will be employed to maintain the integrity of our results. A per-protocol analysis will also be performed to complement the primary intention-to-treat analysis. While the intention-to-treat analysis preserves the advantages of randomisation and reflects real-world implementation challenges, the per-protocol analysis may help assess the true effect of receiving the intervention as intended. Given the negligible planning costs and absence of adverse effects, the intervention may still be considered clinically relevant even if statistical significance is only observed in the per-protocol population.

Characteristics will be reported with numbers, percentages and means with standard deviations or medians with interquartile range, as appropriate. Differences will be calculated using appropriate tests. Appropriate regression analyses will be conducted according to advice from a research statistician. Threshold for significance will be *P* < 0.05.

Readmission and mortality will be calculated and compared as relative risks. We will conduct an interim analysis after 1 year to adjust the time length of the study and to assure that one group does not have a significantly higher mortality rate or readmission rate than the other, which are the stopping criteria. The outcomes examined in the interim analysis will be 30-day mortality and 30-day readmission rate. The interim analysis will be conducted on data masked by a third party to ensure blinding, and the data will not be unblinded unless there is a significant difference in mortality, which is the only stopping criteria. The interim analysis will be conducted after 13 months have passed, i.e. January 2024.

The financial costs analyses will be conducted under supervision of a health economist, [name]. We will analyse our data including time spent by the health professionals and estimate intervention cost per participant, which will be compared to an estimated daily cost of admission and the estimated avoided readmission days.

Qualitative analysis will be conducted to assess user perspectives. This will be conducted as a separate parallel study by [name] [name].

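### The plan lets a per-protocol-only result support clinical relevance; if that population is defined by receipt of the visit, the comparison is biased towards the visit

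*Protocol article*

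**What the plan says.** Under Statistical analyses, intention-to-treat is the primary analysis and a per-protocol analysis complements it. The per-protocol analysis is meant to help show the effect of the visit when it is delivered as planned. The same paragraph adds that "the intervention may still be considered clinically relevant even if statistical significance is only observed in the per-protocol population", on the ground that planning costs are negligible and adverse effects absent. The threshold is given by "Threshold for significance will be" P < 0.05.

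The primary outcome in Table 2 is acute readmission within 30 days, counted from discharge. The visit comes later. The Aim describes a "home visit 2–5 days after discharge", and the abstract and Table 1 also speak of days. Recruitment and enrolment describes a visit "which is planned to take place 2–5 working days after the day of discharge", and the Intervention section also says working days. Controls receive a usual discharge only.

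On timing, the Background reports that "the median number of days until readmission is nine". The Discussion says that most acute readmissions fall in the first week.

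**The concern.** The outcome clock starts at discharge, but receipt of the visit can be established only some days later. An intervention participant must generally stay alive and out of hospital until then to be visited at home. A control has no visit to miss. A population defined by receipt of the visit would therefore exclude participants because of the outcome itself, and in one arm only. This is immortal-time bias, and it favours the visit.

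The per-protocol analysis would be a minor matter if it stayed supportive. The quoted sentence gives it more weight: after a randomised comparison that shows nothing, significance in this population alone may still be read as clinical relevance. The abstract says that a positive effect may lead to scale-up to other departments and to guidelines, so the reading of such a result has consequences.

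**Working it through.** **Inputs from the article**
- Control risk: "a current readmission rate of 19% (control group").
- Planned effect: "an expected 28% reduction by the intervention, the readmission rate in the intervention group is (19 − (19 × 0.28)) 13.68"%, a relative risk of 0.72.
- Sample size: 763 per arm, obtained "using a 2-proportions with 2-sample equality power test", 1:1 allocation, α = 0.05 (taken as two-sided), 80% power.
- Median time to readmission: 9 days.

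**Plan's own figure.** The pooled two-proportion formula for 19% against 13.68% gives 758 per group and the unpooled one 755. Power at 763 is 80.3%. The stated 763 is reproduced closely enough to serve as the base.

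**Assumption on timing.** The article gives a median but no distribution. I take readmission times as exponential, truncated at 30 days:

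F(t) = (1 − e^(−λt)) / (1 − e^(−30λ)), with F(9) = 0.5, so λ = 0.0600 per day.

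This gives F(2) = 0.136, F(5) = 0.311 and F(7) = 0.411. With a constant rate up to the median instead (t/18), the shares are 0.111, 0.278 and 0.389, so the shape matters little once the median is fixed at 9.

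**Share of readmissions before the visit, f.** For visits spread evenly from day a to day b, f is the average of F over that window:

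f = [1 − (e^(−λa) − e^(−λb)) / (λ(b − a))] / (1 − e^(−30λ))

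- Days 2–5: f = (1 − 0.8116) / 0.8349 = 0.226
- Days 2–7: f = (1 − 0.7661) / 0.8349 = 0.280

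Five working days can span seven calendar days, hence the second window.

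**Null effect, one-sided exclusion.** Both arms have risk p = 0.19. If a share f of the intervention arm's readmissions is dropped, its apparent risk is q = p(1 − f) / (1 − pf), among 763(1 − pf) participants.

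- Days 2–5: q = 0.1471 / 0.9571 = 0.154, RR 0.81, 730 left
- Days 2–7: q = 0.1368 / 0.9468 = 0.144, RR 0.76, 722 left

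The chance of significance in favour of the visit is Φ[((p − q) − 1.96·SE₀) / SE₁], where SE₀ is the pooled and SE₁ the unpooled standard error.

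- Days 2–5: Φ[(0.0363 − 1.96 × 0.01955) / 0.01949] = Φ(−0.10) = 46%
- Days 2–7: Φ[(0.0455 − 1.96 × 0.01940) / 0.01931] = Φ(0.39) = 65%

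Repeated simulations agree (45–46% and 64–66%). Significance in the per-protocol set but not in intention-to-treat, the case that the sentence covers, occurs in about 43% and 63% of simulated trials. Intention-to-treat gives about 2.5% in the same direction.

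**Half of the early readmissions still visited and kept.** f becomes 0.113 and 0.140:

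- Days 2–5: q = 0.172, Φ[(0.0178 − 1.96 × 0.01983) / 0.01982] = 14%
- Days 2–7: q = 0.168, Φ[(0.0222 − 1.96 × 0.01976) / 0.01974] = 20%

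**Sensitivity to f** (763 per arm):

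| f | spurious RR | false benefit |
|---|---|---|
| 5% | 0.96 | 6% |
| 10% | 0.92 | 12% |
| 20% | 0.83 | 37% |
| 30% | 0.74 | 72% |

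**Same exclusion in both arms.** Simulated under the null, this brings the rate back to 2.3–2.7%.

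Deaths before the visit are not modelled. They would be excluded in the same one-sided way.

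**The case against.** The strongest objection is that the article never says who is in the per-protocol population. Such definitions are commonly left to an analysis plan, which is not shown and could set a symmetric rule. This stands. A reader might infer that the plan drops early-readmitted intervention patients and keeps the matching controls. The documents do not say so, and every figure above is conditional on a definition by receipt of the visit. The sentence about a per-protocol-only result, however, is printed and does not depend on a later document.

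Second, intention-to-treat stays primary and the sentence says only that relevance may be considered. A reader might infer that the trial's false-positive rate is 46% to 65%, or that per-protocol significance is by itself declared sufficient. Neither is supported: the primary test keeps its error rate. The fault lies in the interpretation that the plan permits.

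Third, a median of nine days does not fix how many readmissions precede days 2–5, and a stay of 12 hours already counts as a readmission, so some of these patients could be home again and visited. Both points stand. Keeping half of them lowers the rates to 14–20%, still well above 2.5%. If the Discussion's first-week statement were the right one, the early share would be larger than assumed here.

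Fourth, it is tempting to say that the artefact equals the planned effect (RR 0.72). That needs f of about 33%, as when visits cluster around day 5 or later. Spread over days 2–5 the spurious RR is about 0.81.

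Finally, negligible planning cost does not strictly contradict Outcome 7, which concerns the cost of the intervention and possible savings. But the justification is still presumed before cost and mortality results exist, and it does not bear on bias in the effect estimate.

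**Conclusion.** The concern holds in conditional form. The article permits a claim of clinical relevance from a population that, if built from its stated aim, is selected on the outcome in one arm.

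The size rests on assumptions that the article does not settle: no true effect, 19% in both arms, 763 per arm, exponential times with median 9, and the share of early-readmitted participants who are dropped. Within these, the chance of a false significant benefit runs from about 14% (half kept, days 2–5) to about 65% (all dropped, days 2–7), against 2.5% for intention-to-treat. It would approach the nominal rate only if about 5% or fewer of all readmissions were removed in this way, or if the rule were the same in both arms.

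**What to change.** 1. Delete the sentence that allows clinical relevance on per-protocol significance alone, together with its justification. State that the effectiveness conclusion rests on the intention-to-treat comparison only.
2. Keep any per-protocol analysis as supportive. Do not exclude intervention participants because of an event before the visit unless the same rule applies to controls.
3. If an estimate of the effect of the visit itself is wanted, use one of these and state its limit:
   - A complier-average estimate with randomisation as the instrument. It assumes that assignment acts only through the visit. The Discussion doubts this, because participants and home care staff who expect a visit may hold back from contacting the primary care physician.
   - A landmark applied on the same day to both arms. A landmark at the end of the window removes readmissions triggered at the visit, which the Intervention section allows for, and these arise in the intervention arm only. It should be accompanied by a landmark at the start of the window, or by a sensitivity analysis over landmark days. Participants readmitted between the landmark and their visit stay in.
4. Reconcile the passages that give the window in days with those that give it in working days, since they decide who counts as visited as planned.

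The cost is wording. Visit data, deaths and readmissions are already collected, and time to readmission is already an outcome. What is lost is a second route to a positive claim.

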### Study design

The study is a single-centre two-arm parallel group randomised controlled trial with an aim to show superiority. It will utilise permuted block randomisation without stratification. Distribution will be equivalent between the two groups. The study will be conducted over approximately 24 months.

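### The interim analysis has two contradictory stopping rules; if 30-day readmission is one of the criteria and is tested at P<0.05 at both looks, its type I error is about 8% instead of 5%

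*Protocol article*

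**What the plan says.** All the interim text stands in one paragraph of the protocol article, under Statistical analyses.

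- Purpose: "We will conduct an interim analysis after 1 year to adjust the time length of the study". The same sentence adds a comparison of the arms, to "assure that one group does not have a significantly higher mortality rate or readmission rate than the other, which are the stopping criteria".
- Both 30-day mortality and the 30-day readmission rate are examined at this look.
- The data are masked by a third party and are not unblinded "unless there is a significant difference in mortality, which is the only stopping criteria".
- Timing: after 13 months, in January 2024. Study design gives a total duration of about 24 months.

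The preceding paragraph gives the only significance level: "Threshold for significance will be *P* < 0.05". The interim paragraph speaks of significance without a level of its own. Under Analyses of primary and secondary outcomes, 30-day acute readmission is named as the primary outcome. The sample size calculation uses an alpha of 0.05 and makes no allowance for an interim test. Trial status dates the protocol version 15 April 2024.

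**The concern.** The two sentences describe different trials. Under the first, a significant readmission difference at the interim ends the study. The wording has no direction (one group against the other), so a difference in favour of the intervention would meet it as well as one against. The primary hypothesis is then tested twice. Under the second, readmission is looked at but cannot stop the trial, and the primary hypothesis is in effect tested once.

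At stake is whether the 5% error rate assumed in the sample size calculation holds for the primary outcome. There is also a reporting problem: the version carrying both rules is dated after the planned look, so a reader cannot tell which rule governed it.

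**Working it through.** **Inputs.** From the protocol article: control readmission 19%; 28% relative reduction, so 0.19 × (1 − 0.28) = 0.1368; alpha 0.05; 0.80 (labelled β but used as power); 1:1 allocation; 763 per group; interim at 13 months of about 24. Assumption: information accrues evenly, so the information fraction is t = 13/24 = 0.54. Recruitment was uneven, so t from 0.3 to 0.7 is also shown.

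**1. The plan's own figure.** The article states that "the sample size should include 763 in each group, and 1526 patients totally". With p1 = 0.19, p2 = 0.1368, difference 0.0532 and mean 0.1634:

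- Unpooled: n = (1.960 + 0.842)² × (0.1539 + 0.1181) / 0.0532² = 754.3, so 755 per group.
- Pooled variance under the null: 758 per group.
- One-sided 0.05: 597 per group.

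The stated 763 fits a single two-sided test at 0.05 with 80% power. The full 5% is assigned to one final test.

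**2. First rule: readmission can stop the trial.** The interim and final z-statistics are bivariate normal with correlation √t. The two-sided error is P(|Z1| > 1.96 or |Z2| > 1.96) under the null. A false claim of benefit is P(Z1 > 1.96 or Z2 > 1.96), with Z positive for benefit.

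| t | √t | two-sided error | false claim of benefit |
|---|---|---|---|
| 0.3 | 0.548 | 8.9% | 4.5% |
| 0.5 | 0.707 | 8.3% | 4.2% |
| 0.54 | 0.736 | 8.2% | 4.1% |
| 0.7 | 0.837 | 7.6% | 3.8% |

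The nominal values are 5% and 2.5%.

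**3. Second rule: mortality alone can stop the trial.** Simulation under the null with 2 million replicates at t = 0.54: stop if the mortality |Z| > 1.96. Readmission is tested at the interim if the trial stops and at the end otherwise, always at 1.96. For a mortality–readmission correlation of 0, 0.3 and 0.5, the readmission error is 5.0%, 5.1% and 5.3%. The chance of a false stop is 5.0%.

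**4. What restores 5% if readmission stays a criterion.** At t = 0.54, a Lan-DeMets boundary of O'Brien-Fleming type gives interim P<0.0046 (critical value 2.83) and final P<0.0485 (critical value 1.973). Overall two-sided error: 5.0%.

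**5. Cost in power.** At 763 per group the expected final z is 0.0532 / √((0.1539 + 0.1181)/763) = 2.82. A single test has power Φ(2.82 − 1.96) = 80.4%. With the two-look boundary, 1 − P(Z1 < 2.83 and Z2 < 1.973), where Z1 has mean 2.82 × 0.736 = 2.07, is 80.2%.

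**6. Lowering only the final threshold.** If the interim test was made at 0.05 and only the final level is lowered to 0.0485, the overall error at t = 0.54 is 8.1%, almost unchanged from 8.2%.

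**The case against.** The best defence is that the second sentence is later, more specific and uses the word only. Read that way, mortality governs and the primary test keeps its level. It can be added that P<0.05 appears once, as a general threshold in the paragraph on characteristics and regression, and that interim boundaries commonly sit in an analysis plan, which is not shown.

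Much of this stands. The absence of a boundary in a condensed article is not in itself an error, and the inflation depends on which rule applied. But the contradiction is in what the article does state, about a look at its primary outcome, and an unseen plan does not correct published text.

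Three stronger readings are tempting and not supported:

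- **The false-positive risk is well above 5% whatever rule applied.** It is about 8% under the first rule only.
- **Study length will respond to the observed arm difference.** The article does not say what drives the adjustment. The timing problems it reports are beds, staffing and patient flow. Masking the group labels would not by itself protect the error rate if the arm difference were used, but nothing says it is.
- **Adding 90-day readmission, which Table 2 also lists as primary, makes the error larger still.** That needs a 90-day rate the article does not give, and it is a separate question.

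**Conclusion.** The contradiction holds in full and has to be reconciled. Its statistical consequence is conditional. With readmission as a stopping criterion at 0.05 at both looks, the two-sided type I error for the primary outcome is about 8.2%, and the range of 7.6% to 8.9% shows that this depends little on when the look falls. With mortality as the only criterion there is no material inflation.

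The figures rest on three assumptions: the one stated threshold also defines significance at the interim, the final test is two-sided at 0.05, and information is roughly proportional to calendar time.

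**What to change.** Reconcile the two sentences to one rule and state the threshold used at the interim. Either of two forms protects the primary test:

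1. Readmission is not a stopping criterion. Study length is adjusted only from recruitment and from the readmission rate pooled over both arms. The final test stays at 0.05.
2. Readmission remains a criterion with an alpha-spending boundary, for example O'Brien-Fleming type at information 0.54: interim P<0.0046, final P<0.0485, recalculated for the actual fraction.

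The interim threshold for the mortality check is for the sponsor to choose and state. A stricter level lowers the chance of a false stop but also the sensitivity to harm, and the article gives no 30-day mortality rate from which to weigh the two.

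Because the look was planned for January 2024, report which rule and threshold were applied, whether readmission was compared between arms, and whether that comparison influenced continuation or study length. If readmission was a stopping criterion at P<0.05, say so with the resulting error rate, since a lower final threshold alone does not repair it.

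Cost: wording and a short disclosure. The first form gives up readmission as a reason to stop. The second costs about 0.2 percentage points of power. If the look has already taken place, neither form can be applied prospectively, and the disclosure is then the main remedy.

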At the visit, the participant, the geriatric nurse and the community nurse conducts a systematic assessment of the participant’s health and register any health-related problems. The assessment is conducted using a standardised Danish tool designed specifically for this purpose (Fælles Sprog III (FS-III) *(In English: Common Language III)*). Only a subsection of the tool, i.e. the parts covering mental well-being and bodily functions is used (“Helbredstilstande” (*In English: Health conditions*)). The tool is well known and used in the Danish home care system [35]. The Fælles Sprog III data is collected for the sole purpose of ensuring a systematic assessment.

For each item in the FS-III the geriatric nurse notes any changes in the participants’ health status, and whether the care plan has been followed, or deviations have been made. Adjustments to the care plan are made and noted accordingly. If there is any cause for concerns regarding the participant’s health compared to the time of discharge the geriatric nurse carries out vital status assessments. Further assessment by ultrasound bladder scan and/or bedside analyses of blood samples for C-reactive protein and electrolytes is based on the geriatric nurse’s clinical judgement. If the geriatric nurse finds it relevant, a geriatrician from G-OUH may be contacted by video. The geriatrician is thus able to communicate with the participant and the geriatric nurse, get the on-site clinically objective results, and finally make a clinical decision. If needed, the participant can be assessed the following day in the geriatric outpatient clinic or be acutely readmitted to the AMU.

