### Study outcome

The study outcomes are listed in the table below. Overall, we have several main focus areas:

The primary aim is to examine whether an early follow-up visit carried out simultaneously by a geriatric nurse and a community nurse can remedy a recently discharged participant’s health problems related to the hospital admission and reduce readmission. As such, the main outcome is 30 days acute readmissions. A readmission is defined as any hospital visit with a LOS of 12 h or longer, as this is in accordance with the definition of acute readmission by the Danish National Health Services [38]. Other aims include the use of in-home clinical assessment and use of POCT to understand their value in the clinical assessment, and their feasibility in an in-home setting. In addition, user perspectives on the home visit are a central outcome covering participants, community nurses, the geriatric nurses and the geriatrician. Other outcomes are the most common post-discharge health-related problems that arise or become apparent in the first days after discharge. Finally, health economic analysis will be carried out (Table 2).

**Table 2 Tab2:** Project outcomes

Outcome		Outcome measure

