***Secondary outcomes***		
Outcome 3	Mortality (1 year)	Proportion of participants deceased within one year
Outcome 4 Outcome 5	Time to Readmission Days alive out of hospital	Proportional hazard model of readmission with a total duration of 1 year and median time to readmission estimated by Kaplan–Meier method Days spent alive out of the hospital within 30 and 90 days from discharge
Outcome 6	Clinical assessments/POCT measurements and their association to decision making	Regression analysis of the association between conducting a clinical measurement (e.g. Saturation, temperature, Sodium, CRP) or POCT analysis and the risk of readmission
Outcome 7	Costs associated with the intervention	Analysis of the costs associated with the intervention and potential savings from the result of the intervention
Outcome 8	User perspectives among involved participants and professionals	Analysis of questionnaires and focus group interviews with involved groups, including participants, community nurses, geriatric nurses, geriatric physician, and primary care physician

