### Data collection

Data will be collected at several points. The data will all be saved and stored in a secure database (REDCap). All personnel involved will be trained data collection.

Before the participant is invited to join the study, data is gathered on eligibility (i.e. diagnosed moderate to severe dementia, residence location to identify citizens of Odense Municipality, and type, use of home care, terminal diseases and presence of delirium).

Before discharge, data is gathered from the participants’ electronic medical records regarding discharge diagnoses, LOS, medication, medical history and Barthel ADL score [39]. A Clinical Frailty Score [40] is assessed by a geriatric nurse.

All data collected during the follow-up visit is registered in our database, including the data gathered in the FS-III survey, vital status and POCT results. The vital parameters and POCT results will be used to understand their influence on the clinical decision making.

The data collected during the follow-up visit will be filled directly into pre-defined fields in REDCap and will help ensure that all the necessary data is collected.

All participants, controls and interventions will receive a questionnaire, which is a modified version of a previously validated questionnaire [41]. At the time of randomisation, both groups will be asked about their satisfaction with the treatment, care and hospitalisation in general, as well as if they feel safe being discharged. A follow-up questionnaire will be administered to both groups by telephone. Data will be transferred to REDCap manually. The questionnaires will be administered by project coordinators who are not involved in the clinical care of the patients.

Data on death and readmissions will be collected from electronic medical records for 1 year after the allocation date for each participant.

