### Analyses of primary and secondary outcomes

The primary outcome is 30-day acute readmission. We will use relative risks to compare the readmission rates in the two groups. Relative risk for other readmission time frames will also be calculated to improve comparisons with other studies.

Competing risk of death will be considered in our analyses, as it can skew the results. Partially due to this, days out of hospital will also be calculated as it is less affected by the competing risk of death than a binary readmission outcome.

We will also calculate the relative risks for 30-day mortality.

A proportional hazard model will be used to explain the time to readmission. This will be done using the Cox regression model. Moreover, median time to readmission will be estimated by the Kaplan–Meier method.

We will include relevant patient characteristics that are known risk factors in our statistical analyses, e.g. multimorbidity, polypharmacy and length of stay.

Throughout the analyses, we will adjust for participants that were already readmitted at the time of recruitment. Separate analyses will be done for patients that already received the intervention, as there may be a residual effect of the intervention.

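### The cost comparison credits avoided readmission days but does not cost outpatient and under-12-hour hospital contacts in both arms

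*Protocol article*

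**What the plan says.** Table 2 of the protocol article describes Outcome 7 as "Analysis of the costs associated with the intervention and potential savings from the result of the intervention". The section Statistical analyses gives the method: "We will analyse our data including time spent by the health professionals", and then "estimate intervention cost per participant, which will be compared to an estimated daily cost of admission and the estimated avoided readmission days". A health economist will supervise the work.

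Four other statements bear on this comparison:

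- **Intervention:** if needed after the visit, "the participant can be assessed the following day in the geriatric outpatient clinic or be acutely readmitted to the AMU".
- **Study outcome:** "A readmission is defined as any hospital visit with a LOS of 12 h or longer".
- **Data collection:** "Data on death and readmissions will be collected from electronic medical records for 1 year after the allocation date for each participant". No other hospital use is named as follow-up data.
- **Analyses of primary and secondary outcomes:** "Competing risk of death will be considered in our analyses, as it can skew the results". Partly for that reason the plan adds Outcome 5, "Days spent alive out of the hospital within 30 and 90 days from discharge".

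The Discussion expects the health economic result to weigh in decisions on adopting the visit in other settings.

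**The concern.** The section Statistical analyses names what goes on each side of the comparison. The saving side holds readmission days valued at a daily admission cost. The trial's own pathway can produce hospital care that is not a readmission day: a next-day clinic assessment, or an acute contact that ends before 12 h. If the visit replaces an admission with one of these, the whole admission is credited and the replacement is not set against it across the arms.

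Death also bears on the measure. A participant who dies accrues no further readmission days, so the count of avoided days depends on survival as well as on the effect of the visit. The protocol recognises this for the readmission analyses but does not connect the cost comparison to mortality or to days alive out of hospital.

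At stake is whether a reported net saving would be a saving to the hospital or partly a move of cost between types of contact.

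**Working it through.** **1. Where each kind of care falls in the stated comparison**

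| Care | Source | Place in the comparison |
|---|---|---|
| Staff time for the visit | Statistical analyses | Intervention cost |
| Hospital stay of 12 h or longer | Study outcome | Readmission days, both arms |
| Next-day outpatient assessment | Intervention | Not named; could be booked as intervention cost, in one arm only |
| Hospital contact under 12 h | Study outcome (excluded from readmission) | Not named in either arm |

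Booking triggered clinic visits as intervention cost would still leave the control arm's outpatient and short contacts uncosted. On either reading, no between-arm total of hospital contacts is formed.

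**2. The credit at the planned effect**

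The cost outcome states no figure of its own. The sample size section gives 19% readmission in the control group and a 28% relative reduction: 19 × (1 − 0.28) = 13.68%, as stated. With two-sided α of 0.05 and 80% power, the usual two-proportion formula gives 758 per group against the stated 763, so the planning rates are reproduced.

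Assume that a readmission lasts as long as the mean ward stay of 6.1 days (Setting and study population). This is a proxy, because the article gives no readmission length.

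Credit = (0.19 − 0.1368) × 6.1 = 0.0532 × 6.1 = 0.325 bed-days per intervention participant, or about 248 days per 763.

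**3. Avoided stays replaced by an uncosted contact**

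Let a share *s* of avoided readmissions become one uncosted contact worth *c* bed-days. The share of the credit that is wrong is *s* × *c* / 6.1.

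- *s* = 10%, *c* = 0.25: 0.4%
- *s* = 50%, *c* = 1: 8.2%
- *s* = 100%, *c* = 1: 16.4%

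**4. Any between-arm difference in uncosted contacts**

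Let *r* be the contact rate in the intervention arm minus that in the control arm. The offset is *r* × *c* / 0.325.

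- *r* = 2%, *c* = 0.25: 0.005 / 0.325 = 1.5%
- *r* = 10%, *c* = 0.5: 0.05 / 0.325 = 15%
- *r* = 20%, *c* = 1: 0.20 / 0.325 = 62%

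The top of this range means 20 extra contacts per 100 participants against 5.32 avoided readmissions per 100, so most of those contacts would be in people who would not have been readmitted anyway. If *r* is negative, the stated comparison understates the saving.

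**5. Survival**

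Suppose each excess death in the intervention arm removes the control group's average expected readmission days, 0.19 × 6.1 = 1.159. For an excess *d* in 30-day mortality, the apparent saving is 1.159 × *d*.

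- *d* = 0.5 points: 0.006 bed-days, 1.8% of the credit
- *d* = 5 points: 0.058 bed-days, 18% of the credit

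Lower mortality in the intervention arm reverses the sign. The values of *s*, *c*, *r* and *d* are all assumptions; the documents give none of them.

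**The case against.** The article gives the cost analysis two sentences under a health economist's supervision. Cost items and unit costs are commonly left to a fuller plan, and silence is not exclusion. This stands for unit costs and detail. It does not cover the comparison itself, which the article states and which has only readmission days on its saving side.

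Three stronger readings are tempting, and the documents do not support them.

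- **That only the visit is costed.** The list of data is open-ended, and Table 2 speaks of costs associated with the intervention, so a clinic assessment triggered by the visit could be included. What remains is the asymmetry shown in the working.
- **That the comparison leans towards a saving.** Control participants also have outpatient and short contacts, and only the difference between arms matters. The Discussion suggests that the visit may prevent contacts with the primary care physician, a possible saving that is also not credited. An AMU stay of 12 h or longer does count as a readmission. The direction is not established.
- **That deaths are counted as savings.** No text credits deaths. The effect needs higher mortality in the intervention arm, which nothing in the documents suggests. The plan promises to consider competing death and already includes mortality and days alive out of hospital. What is missing is the link between these and the cost result.

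**Conclusion.** The point holds in a limited form. The stated method for Outcome 7 does not cost outpatient and under-12-hour hospital contacts symmetrically between arms, and it is not tied to survival or to days alive out of hospital. Replacing an admission with such a contact would be credited as a full saving.

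The size and net sign cannot be settled from the documents, which give no unit costs, contact rates or mortality rates. Under the assumed inputs the effect runs from negligible to more than half of the credited bed-days. The pure replacement effect stays at or below 16.4% if each contact costs no more than one bed-day. These figures show sensitivity and are not estimates of bias. They also rest on 6.1 days as a proxy for readmission length.

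This is a secondary outcome, and the primary readmission analysis is unaffected. It is still worth correcting, because the protocol expects the economic result to influence adoption elsewhere.

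**What to change.** In Statistical analyses, define Outcome 7 as the intention-to-treat difference between the randomised arms in mean cost per participant over 30 and 90 days. The cost should consist of:

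- the intervention cost; and
- all hospital contacts of any length in both arms: inpatient stays, AMU contacts under 12 h and outpatient visits.

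Take the contacts from the hospital records and administrative system that Recruitment and enrolment already names as data sources, and add outpatient and short contacts to the follow-up items under Data collection. Report the cost difference beside the mortality and days-alive-out-of-hospital results already planned. If municipal and primary care costs are unavailable, state as a limitation that they are not included.

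The price is modest extra data extraction and a somewhat longer economic analysis, and the reported saving may turn out less favourable. Recruitment, treatment and the primary analysis do not change, and the definition can be fixed before the masked data are analysed.
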